## Abstract

**Background:** Worldwide sugar consumption has tripled during the last fifty years. High sugar intake is associated with weight gain, increased incidence of diabetes and has been linked with increased cardiovascular mortality. Reducing the health impact of dietary sugar and poor quality carbohydrate intake is a public health priority. IminoNorm®, a proprietary mulberry leaf extract (ME) may reduce blood glucose responses following dietary sugar and carbohydrate intake by reducing absorption of glucose from the gut. Previous research has shown that ME can reduce blood glucose and improve insulin responses in healthy subjects and also in subjects with raised fasting blood glucose levels. Mulberry leaf has an excellent safety profile. This pilot study will test a novel safe water soluble product in normoglycaemic adults in the UK to determine if it can reduce glucose absorption without increasing plasma insulin concentration.

**Methods/Design:** The trial will be a double blind, individually randomised, four-arm single dose crossover design to test the effect of three doses of ME in order to determine efficacy, dose response relationship and gastrointestinal side effects with respect to placebo. A total of 40 subjects will participate in this study and attend for four visits receiving each of the four interventions in random order.

**Discussion:** We aim to test the evidence that mulberry leaf extract can reduce blood glucose without a disproportionate increase in blood insulin responses in healthy individuals in a high-quality research study based in the UK. It is hoped that this will lead to further randomised controlled trials and an effective dietary supplement to lower blood glucose concentrations.

**Trial Registration:** ISRCTN: ISRCTN 14597438 (21/04/2015)

**Keywords:** Mulberry, Glycaemic Response, Insulinaemic Response

## Background

Excess calorie intake including those from sugar can make a significant contribution to becoming overweight [1, 2] and thus increase the risk of developing Type 2 diabetes mellitus (T2DM) [3, 4]. In 2013 a large long-term European study investigating the effect of diet on health [5] found an association between the amount of sugary soft drinks people had and their risk of Type 2 diabetes. In this study weight gain had a large effect on diabetes risk and sugary drinks had a small effect on diabetes risk even after Body Mass Index (BMI) was corrected for. The global rise in T2DM is linked to the metabolic syndrome (dyslipidemia, hypertension, insulin resistance), and obesity is thought to be one of the greatest risk factors for metabolic syndrome and T2DM [6]. Dietary sugars and carbohydrates play a significant role as calories from these foods promote fat storage and hunger [7]. A recently completed review of nutrition and its impact on T2DM

concluded that dietary restriction of carbohydrate intake is the single most effective approach to manage T2DM [8]. It is estimated that more than 1 in 17 people in the UK have diabetes (diagnosed or undiagnosed) [9] and thus reducing the health impact of dietary sugar and poor quality carbohydrate intake is a public health priority. Herbal agents could be quite effective in the management of carbohydrates in the normal diet and in reducing post-prandial blood glucose [11].

Mulberry (*Morus alba*) leaves have been used in traditional Chinese medicine (TCM) for several millennia and its use was first recorded in around 500AD in the *Divine Husbandman's Classic of the Materia Medica* [10]. It has also been used for more than 750 years in Japan as an infusion tea [11]. It is used by some human communities for food purposes and in several Asian countries as a herbal tea. Reports have shown that the leaves are nutritious and non-toxic [12]. The Chinese Ministry of Health and the Taiwanese Bureau of Food Safety recognise *Morus alba* leaves as both a food and a medicine [13]. Mulberry leaf extracts (ME) have a long history of safe use globally for normalizing post-prandial blood glucose, and it is thought that iminosugars such as 1-deoxynojirimycin (DNJ), a reversible, competitive natural  $\alpha$ -glucosidase inhibitor, are the main active components responsible for the activities [11].

ME can significantly reduce the peak blood glucose levels and the insulin response levels (Kimura, *et al.*, 2007; Mudra *et al.*, 2007), providing protection to blood glucose metabolic function of healthy and hyperglycemic subjects [14, 15]. ME can reduce oxidative stress, glucose fluctuations during postprandial periods and more generally, glucose swings triggering effects on oxidative stress. By reducing oxidative stress, ME has the potential to slow down the process of prediabetes to diabetes and diabetes to developing complications [16, 17]. Long-term administration of ME produced a dose-dependent decrease in body weight and hepatic lipid accumulation [17], stimulated skeletal muscle 5'-AMP-activated protein kinase activity acutely without changing the intracellular energy status [18], suppressed the elevation of postprandial blood glucose and cholesterol in humans [14] and exhibited potential hypoglycemic and hypolipidemic effects in diabetic patients [19]. Therefore, ME may help reduce blood glucose peaks caused by the ingestion sugary or carbohydrate rich foods and drinks. Mulberry tea has been shown to suppress the postprandial rise of blood glucose levels after 90 minutes of its consumption in T2DM subjects [20].

The aim of this study is to determine the effect of three doses of a proprietary water extract of mulberry leaves standardized to contain 5% DNJ (IminoNorm®) versus placebo on blood glucose and insulin responses when co-administered with 50g maltodextrin in normoglycaemic healthy adults. We also aim to determine the gastrointestinal tolerability of the mulberry extract using both normal (250mg IminoNorm® containing 12.5mg DNJ), half (125mg IminoNorm® containing 6.75mg DNJ), and double (500mg IminoNorm® containing 25mg DNJ) the normal dose. Maltodextrin is a dietary starch with a high glycaemic index, is commonly added to many foods and beverages and has been used as a test carbohydrate in similar studies [21]. We hypothesise that ME will reduce glucose excursions without causing a disproportionate increase in insulin release and thus its ingestion may confer protection against the development of diabetes, although further trials would be required to determine its long-term efficacy.

## **Methods / Design**

### ***Objectives***

The primary objective is to determine the effect of three doses of mulberry-extract (IminoNorm®) versus placebo on blood glucose and insulin responses when co-administered with 50g maltodextrin in normoglycaemic healthy adults. We also aim to determine the gastrointestinal tolerability of the mulberry extract using both normal (250mg IminoNorm® capsule containing 12.5mg 1-deoxynojirimycin), half (125mg IminoNorm® containing 6.75mg DNJ), and double (500mg IminoNorm® containing 25mg DNJ) the normal dose. The ME (IminoNorm®) is provided by Phynova Group Ltd, UK.

### ***Hypothesis***

Our primary hypothesis is that an appropriate dose of mulberry extract co-administered with oral maltodextrin will reduce the incremental area under the curve for plasma glucose concentration over 120 minutes in normoglycaemic adults in a dose-dependent manner when compared to co-administration with placebo. Our secondary hypothesis is that mulberry extract co-administered with oral maltodextrin will not disproportionately increase the incremental area under the curve for plasma insulin concentration over 120 minutes in normoglycaemic adults compared to co-administration with placebo.

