### ***Outcomes***

Primary outcome:

iAUC for plasma glucose concentration over 120 minutes.

Secondary outcomes:

- iAUC for plasma insulin concentration over 120 minutes.
- Gastrointestinal tolerability – abdominal bloating may be experienced due to reduced carbohydrate absorption. Gastrointestinal symptoms will be measured via questionnaire for 24 hours following each study visit. Subjects will use a 5-point scale to rate stool consistency for each bowel movement for 0-24 h after the study product consumption. The five-point scale includes: 1=watery, 2=loose/mushy, 3=soft, 4=formed, 5=hard. Frequency and intensity will be set to a 10-centimeter (cm) line scale (0 representing "Absent" for frequency and "Usual" for intensity; 10 representing "More than usual" for frequency and "Severe" for intensity).

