## ***Statistical Analysis***

This is the first rigorous study of IM and should therefore be considered as a pilot study from a statistical perspective. We will calculate the incremental area under the curve for all 4 study products and compare using repeated measures ANOVA to determine whether there is a statistically significant difference in plasma glucose levels and in secondary outcome measure over the 120 minute period. All models will control for the possible confounding effects of sex and BMI. The presence/absence of gastrointestinal symptoms in the 24 hours following the study visit will be assessed using logistic regression models. We anticipate a low likelihood of missing data (as sufficient blood is taken for a second analysis to be performed if the first analysis fails) and our glucose values will be measured in real time. We anticipate monophasic or biphasic glucose and insulin curve responses and will use a 2nd order interpolation method for missing data, provided that no other data is missing from the two neighbouring time points at either side of a missing data set and that the baseline and end data values are obtained. If the baseline or end points are missing or more than one data point within five neighbouring time points, this data set will be deemed unsuitable and not be included in the analysis.

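### The insulin hypothesis claims no disproportionate rise, but the only stated analysis tests for a difference and no limit defines disproportionate, so a null result could not support it

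*Protocol*

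**What the plan says.** The Protocol's Hypothesis section words the secondary hypothesis as a negative: the extract, taken with maltodextrin, "will not disproportionately increase the incremental area under the curve for plasma insulin concentration over 120 minutes" compared with placebo. The Background says the same of glucose lowering "without causing a disproportionate increase in insulin release", and the Discussion repeats the idea. None of these places gives a margin, a confidence limit or a ratio to the glucose change that would define disproportionate.

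The Outcomes section lists "iAUC for plasma insulin concentration over 120 minutes" as a secondary outcome. Statistical Analysis gives glucose and the secondary outcome the same treatment: the four products are to be compared by repeated measures ANOVA to look for "a statistically significant difference in plasma glucose levels and in secondary outcome measure over the 120 minute period". It does not say how a non-significant insulin result will be interpreted.

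Two other places differ from this. The background paragraph of the Abstract sets a stricter aim, to "determine if it can reduce glucose absorption without increasing plasma insulin concentration". The Objectives place insulin inside the primary objective, as the effect of three doses "versus placebo on blood glucose and insulin responses when co-administered with 50g maltodextrin in normoglycaemic healthy adults".

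**The concern.** A test for a difference suits the glucose hypothesis, which predicts a reduction. It does not suit a claim that something does not go up by too much. Failing to reject equality does not show that a rise is absent or small, and noisier insulin data make failure to reject more likely. Without a limit, the hypothesis also cannot be contradicted: even a significant rise could be called proportionate.

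The insulin claim is one half of the trial's message (lower glucose without a disproportionate insulin response), and the Discussion says the results will inform a larger trial. If that half rested on a p-value above 0.05, it would be weakest exactly where the data are least informative.

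**Working it through.** **Inputs from the Protocol.** Sample Size gives at least 80% power for a 25% difference in iAUC with 30 participants, derived from a glucose result, and recruitment of 40. Study Design gives a crossover in which every participant takes all four products, so each dose-versus-placebo contrast is within person.

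**Not in the Protocol, so assumed.** The significance level (two-sided 5%), the SD of the within-person difference for insulin (30% to 80% of the placebo mean), and the size of any true rise. Each contrast is treated as a paired t-test on n differences, with non-centrality δ = (true difference / SD) × √n.

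**Step 1: the plan's own figure.** The 80% power cannot be reproduced, because no SD is stated. It can only be solved backwards. With n = 30 and a 25% difference, 80% power requires SD = 47.2% of the placebo mean: δ = (25 / 47.2) × √30 = 2.90, against a critical t (29 df) of 2.045, gives power 0.80. Because the text says at least 80%, 47.2% is the largest glucose SD consistent with it at this significance level. At the same SD, power for a 58% difference exceeds 99.9%, so the plan's two power statements agree with each other.

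**Step 2: chance that a true rise in insulin iAUC is non-significant.** This is P(|T| < critical t), where T is non-central t with n − 1 df. Example: for a 20% rise at SD 47.2% and n = 30, δ = (20 / 47.2) × √30 = 2.32, giving 0.39.

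| SD of difference | True rise | n = 30 | n = 40 |
|---|---|---|---|
| 30% | 20% | 6% | 2% |
| 47.2% | 10% | 80% | 74% |
| 47.2% | 15% | 61% | 50% |
| 47.2% | 20% | 39% | 26% |
| 47.2% | 25% | 20% | 10% |
| 60% | 20% | 58% | 46% |
| 80% | 20% | 74% | 66% |

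**Step 3: what a null result leaves open.** The 95% confidence half-width is t × SD / √n. At SD 47.2% it is 2.045 × 47.2 / √30 = 17.6 points with 30 participants, and 2.023 × 47.2 / √40 = 15.1 points with 40. An estimate just short of significance at n = 30 is therefore compatible with a true rise of about 2 × 17.6 = 35 points.

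**Step 4: would a limit be workable?** Take a true change of zero and require the upper 95% limit to lie below a bound (one-sided 2.5%). These bounds are illustrations only.

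- Additive bound of 25 points, SD 47.2%: δ = 2.90 at n = 30 and (25 / 47.2) × √40 = 3.35 at n = 40. Power is about 80% and 90%.
- Ratio bound of 1.25 on the log scale. The same SD is converted under a lognormal assumption: within-person SD 0.472 / √2 = 0.334, and log-difference SD = √2 × √ln(1 + 0.334²) = 0.46. Then δ = (ln 1.25 / 0.46) × √n, with ln 1.25 = 0.223, gives 2.66 and 3.07. Power is about 73% and 85%.
- Additive bound of 20 points: 80% power needs 46 participants at SD 47.2%, and 20 to 128 across SD 30% to 80%.

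**The case against.** **No rule equates a null result with support.** A reader might infer that a non-significant insulin result would be read as confirming the hypothesis. The Protocol never says so; it says only that the ANOVA will look for a difference. This stands: the risk is that the result could be read that way, since no other criterion is offered.

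**The expected direction is down.** The Background reports that mulberry extract lowers insulin responses as well as peak glucose. A significant fall under the planned test would support the hypothesis properly. This also stands, and it confines the problem to a null result or a rise. The calculations above show what a null result could hide; they do not predict that insulin will rise.

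**The size is borrowed.** The 47.2% is a glucose-based upper bound applied to insulin. At SD 30% the planned test would miss a 20% rise only rarely. In addition, 40 rather than 30 are recruited, and Trial Status says most have completed all visits. This is fair, and it is why the result is given as a range. It does not remove the mismatch, which holds at any SD.

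**The stakes are limited.** Insulin is secondary in both Hypothesis and Outcomes, and Statistical Analysis calls the study a pilot. That argues against treating this as a fatal flaw, a reading the document does not support. It does not make the stated test fit the stated hypothesis.

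**An unseen statistical analysis plan may cover it.** Confidence intervals are often left to that document. Here, however, the Protocol states both the hypothesis and the test, and the two do not match, so this is more than missing detail.

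**Conclusion.** The point holds as a mismatch between hypothesis and analysis. The stated test can support the insulin hypothesis only if insulin falls significantly. On a null result it gives no support, and on a significant rise there is no basis for judging disproportion.

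The size depends on an insulin SD that the Protocol does not give. For an SD of 30% to 80% of the placebo mean and two-sided 5%, a true 20% rise is non-significant in 6% to 74% of trials at n = 30 and 2% to 66% at n = 40. At the 47.2% implied by the glucose power statement, the figures are 39% and 26%.

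The documents do not show that 30 to 40 participants are too few. That depends on a limit and an SD that are both unstated. The primary glucose analysis is unaffected. This should be fixed before unblinding, in proportion to a secondary outcome in a pilot. The differing wording in the Abstract and Objectives is a minor, separate inconsistency.

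**What to change.** Before unblinding:

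1. Report each dose-versus-placebo contrast in insulin iAUC with a 95% confidence interval from the within-participant model.
2. Define disproportionate as an upper limit on that contrast, fixed in advance with a justification. State whether it is a difference or a ratio, because the power differs between the two. The 25% in Sample Size is a glucose-derived difference to detect; it does not by itself justify a tolerable insulin rise.
3. Conclude that there is no disproportionate increase only where the upper confidence limit lies below that bound.
4. If no limit can be justified, present insulin as estimation only and state that non-significance is not evidence for the hypothesis.
5. As a minor tidy-up, align the Abstract's stricter aim and the Objectives' ranking of insulin with Hypothesis and Outcomes, where insulin is secondary.

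This needs no new participants, visits or samples, only wording in the protocol or analysis plan. The cost is that the insulin claim becomes harder to make: even if insulin truly does not change, it may fail to meet the limit.

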### **Study Design**

A double-blind, randomised, repeat measure, crossover design trial will be used to study the glycaemic response (GR) and insulinaemic response (IR) to three products: one reference product and three test products. Participants will act as their own controls, i.e. each participant will test all four products. The trial will be conducted by the Functional Food Centre at Oxford Brookes University. Ethical approval for the study has been obtained from the University Research Ethics Committee (UREC) of Oxford Brookes University, Faculty of Health and Life Sciences, [name]. Participants will be given full details of the study protocol and the opportunity to ask questions. All participants will give written informed consent prior to participation.

### ***Participants***

A sample size of 40 participants will be recruited to allow for any dropouts during the study. Healthy male and female adult participants (aged 18-60 years) will be recruited for the study in order to determine if ME can have an affect on subjects without impaired glucose tolerance.

### ***Exclusion Criteria***

The exclusion criteria of the MULBERRY trial are listed in table 1.

In addition, participants will be excluded if they are unable to comply with experimental procedures or do not follow GR and IR testing safety guidelines.

### ***Suspension Criteria***

All adverse events will be monitored and recorded from the time of the screening visit through 24 hours after treatment visit. Subjects may be excluded or have the study product discontinued if the investigator decides discontinuation of the study product is in the best medical interest of the subject (e.g., due to noncompliance, changes in medications or dietary supplements, an adverse event or serious adverse event, or a change in medical status) or if the subject requests withdrawal from the study.

### ***Sample Size***

A recent study in India (which is yet to be published) in 12 healthy individuals age 18-25 using 250mg ME dose showed a reduction in the glycaemic index of maltodextrin by 58% when compared to placebo. A sample size of 30 would allow over 90% power to detect a difference of a similar size. Being more conservative and allowing for a smaller difference to be detected in the lower concentration doses, 30 participants would still allow at least 80% power to detect a difference of 25% in the incremental Area Under the Curve (iAUC). In order to account for a potential loss to follow up, and the possibility that our sample size may be inaccurate as it is based on a small pilot sample we will therefore recruit 40 participants.

### ***Randomisation***

Researchers recruiting the participants will be unaware of the allocation sequence (concealed allocation). Assignment of participants to a participant number will be done according to their chronological order of enrolment in the study. The allocated participant number will identify the participants and their corresponding intervention sequence. A code break for the randomisation will be kept by the Principal Investigator and will only be broken in terms of a serious adverse event.

### ***Blinding (Treatment / Placebo)***

Four products will be tested in this study - one placebo reference product (four capsules containing 125mg microcrystalline cellulose) and three test products containing different doses of mulberry extract (test product groups receive either 1, 2, or 4 capsules containing 125mg ME, with either 3, 2, or 0 placebo capsules respectively so that participants always take 4 capsules). The study products are double blinded to both investigator and subject. Each test/reference product will be co-administered with 50g maltodextrin dissolved in 250ml water. Products will be produced by Phynova and delivered to the study centre labelled as 'Product variant A', 'Product variant B', 'Product variant C' and 'Product variant D' with sealed envelopes labelled with participant number and the intervention sequence for the respective participant.

### ***Study Period***

In each participant, the reference product and test products will be tested in random order on (four) separate days, with at least a two-day gap between measurements to minimise carry over effects. The study schedule is summarised in Table 2.

### ***Outcomes***

Primary outcome:

iAUC for plasma glucose concentration over 120 minutes.

Secondary outcomes:

- iAUC for plasma insulin concentration over 120 minutes.
- Gastrointestinal tolerability – abdominal bloating may be experienced due to reduced carbohydrate absorption. Gastrointestinal symptoms will be measured via questionnaire for 24 hours following each study visit. Subjects will use a 5-point scale to rate stool consistency for each bowel movement for 0-24 h after the study product consumption. The five-point scale includes: 1=watery, 2=loose/mushy, 3=soft, 4=formed, 5=hard. Frequency and intensity will be set to a 10-centimeter (cm) line scale (0 representing "Absent" for frequency and "Usual" for intensity; 10 representing "More than usual" for frequency and "Severe" for intensity).

## ***Recruitment***

Participants will be recruited following local advertisements and all participants will be given full details of the study protocol and the opportunity to ask questions. All participants will give written informed consent prior to participation and will be paid £10 per visit, on completion of all four visits. This has been determined as an appropriate amount to cover and travel costs and the time spent during each visit.

